**Figure 1 F1:**
[figure not shown]

The patients are followed-up for 5 years.

In case of reoperation for ASIO the procedure is carried out by a third party blinded to the patient's previous antiadhesive treatment: this surgeon evaluates incidence, location, severity, and extent of adhesions. The incidence of adhesions is assigned a severity score of 0 [no adhesions], 1 [filmy thickness, avascular], 2 [moderate thickness, limited vascularity], or 3 [dense thickness, vascularized].

Adverse events [AEs] are collected for the duration of the study, beginning at the time of randomization.

AEs are identified and described by the primary investigators.

In the control group, patients will be treated as in our daily surgical practice.

In the informed consent form, patients receive all the information about the study protocol, confidential data management and they fill up a questionnaire before signing or refuse.

There are not inconveniences caused to the patients. No incentives are planned for the patients regarding the operation or the follow-up.

There are not any additional risks for the treatment and control group: both groups have the standard surgical treatment and follow-up: icodextrin group is an antiadherences fluid with no adverse effects.

All the medical information obtained from the patients are kept confidential among the research scientists conducting the study.

The patients are free to withdraw from the study, whenever they want and without any obligation.

The study is approved by the ethical Committee of the S'Orsola-Malpighi Hospital, Bologna, Italy

The primary endpoints of our study are:

To evaluate the therapeutic role of Icodextrin 4% to reduce ASIO incidence

To reduce adherences rate [in case of reoperation for ASIO]

The onset of any other complications are recorded intraoperatively, postoperatively, at discharge, at 7-days, 1-month, 6-months, every year up to 5 years follow-up.

The primary outcomes are assessed every year [interim analysis] up to 5 years after the last enrolled patient.

The data generated by this study are analysed in two ways. The continuous numerical data are subjected to analysis of variance [ANOVA], this method being applicable to the discrimination of two continuous populations. Discrete data are analysed by the chi-squared test or Fisher exact test, as appropriate. Statistically significant differences between study treatments are based on p < 0.05.

The study takes approximately 2 years for the inclusion period. According to the number of ASIO menaged monthly by each surgeon in our Department, the duration of the inclusion period can be approximately 2 years to reach the number of about 176 enrolled patients.

ASIO is a common disease. Any improvement in this field will benefit many patients reducing the re-operative rate.

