## Introduction

Adhesive small intestine occlusion [ASIO] is an important cause of hospital admission placing a substantial burden on healthcare systems worldwide. Often times, ASIO is associated with significant morbidity and mortality. Postoperative adhesions account for > 40 percent of all cases of intestinal obstruction, with 60 to 70 percent of those involving the small bowel [1]. Of patients who require multiple abdominal operation, 30 to 44 percent have adhesion-related intestinal obstruction [2]. For small-bowel obstruction, the incidence rises to 65 to 75 percent [3]. Mortality rates range from 3 percent for simple intestinal obstructions to 30 percent when the bowel becomes necrotic or perforated [3].

The overall recurrence rate for patients who underwent one operation for ASIO is 18% after 10 years and 29% at 30 years. For patients admitted several times for ASIO, the relative risk of recurring ASIO increased in relation to the number of prior ASIO episodes. The cumulative recurrence rate reached 81% for patients with 4 or more ASIO admissions [4]. In the US, adhesiolysis is responsible for > 300,000 hospitalizations annually, accounting for nearly 850,000 days of inpatient care and $1.3 billion in hospitalization and surgical expenditures [5].

An increasing number of adhesion-reduction agents, in the form of site-specific and broad-coverage barriers and solutions, are becoming available to surgical teams to complement optimal surgical techniques. Icodextrin 4% solution [Adept, Shire Pharmaceuticals, UK] is a high-molecular-weight a-1,4 glucose polymer that is approved in Europe for use as an intra-operative lavage and a post-operative instillate to reduce the occurrence of post-surgery intra-abdominal adhesions [6]. The icodextrin colloid is absorbed slowly, resulting in the retention of the fluid within the peritoneal cavity for more than 4 days. The solution reduces adhesions by a process of hydroflotation, keeping the peritoneal organs and tissues apart during the critical post-surgery period when the patient is at greatest risk of adhesion formation [7]. 1 Icodextrin has an extensive safety profile and has been used as a 7.5% solution in continuous ambulatory peritoneal dialysis [CAPD] for > 50,000 patient-years. In addition, preclinical and preliminary clinical studies have demonstrated the safety and efficacy of Icodextrin 4% solution in the reduction of adhesion formation following abdominopelvic surgery [8].

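### The second primary endpoint compares adhesions only in patients reoperated for recurrent ASIO, a subset selected by the first primary outcome, and should be descriptive rather than primary

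*Protocol article*

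**What the plan says.** All of this stands in the Methods of the protocol article.

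- The text after Figure 1 introduces a list with "The primary endpoints of our study are" and gives two items without ranking: "To evaluate the therapeutic role of Icodextrin 4% to reduce ASIO incidence" and "To reduce adherences rate [in case of reoperation for ASIO".
- The same text fixes when adhesions are seen after treatment: "In case of reoperation for ASIO the procedure is carried out by a third party blinded to the patient's previous antiadhesive treatment". At that operation "this surgeon evaluates incidence, location, severity, and extent of adhesions". The scale runs from 0 to 3: "The incidence of adhesions is assigned a severity score of 0 [no adhesions", with 3 for dense, vascularised adhesions. No second look is described in patients who are not reoperated.
- One significance rule covers everything: "Statistically significant differences between study treatments are based on p < 0.05".
- The opening part of the Methods says that every randomised patient enters the analysis. It sizes the trial on recurrence alone: 50% falling to 25%, 95% confidence, 80% power, 65 analysable and 88 enrolled per group.

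**The concern.** A patient contributes to the second primary endpoint only after a recurrence, which is the first primary event, and then a reoperation for it. Treatment is meant to change who gets that far. If icodextrin prevents some recurrences, the reoperated icodextrin patients and the reoperated controls have been filtered differently, and randomisation no longer makes them comparable. An analysis plan cannot repair this, because the restriction is part of the endpoint's definition.

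The incidence part of the endpoint has a further problem. ASIO is obstruction caused by adhesions, so patients reoperated for it will nearly all have them, whichever arm they were in.

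A primary endpoint supports the headline claim. This one could conceal much of a real benefit, or lend primary status to a chance difference in a few patients.

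**Working it through.** **Inputs from the article.** Recurrence 50% (control) and 25% (icodextrin); 88 enrolled and 65 analysable per group; p < 0.05; 80% power. Two-sided testing is assumed. **Not given, so assumed:** the share of recurrences that is reoperated, and the link between adhesion severity and reoperation.

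**1. The stated sample size.** Two proportions, 0.50 and 0.25, mean 0.375:

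n' = [1.96·√(2·0.375·0.625) + 0.842·√(0.25 + 0.1875)]² / 0.25² = 57.7

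With continuity correction: n = (57.7/4)·[1 + √(1 + 4/(57.7·0.25))]² = 65.4, or 66 rounded up, against 65 stated. 66/0.75 = 88. The sizing is reproduced and is not in question, but it concerns recurrence only.

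**2. Incidence among the reoperated.** If all scored patients have adhesions, the table is 100% versus 100%. Fisher's test then never rejects: power 0 and type I error 0.

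**3. How many patients are scored.** At 88 per group and the planned risks, the count is 88 × risk × share reoperated. The detectable difference at 80% power is 2.80·√(1/n₁ + 1/n₂), in SDs within the reoperated group.

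| Share reoperated | Control | Icodextrin | Detectable difference |
|---|---|---|---|
| 100% | 44 | 22 | 0.73 SD (0.74 by exact t) |
| 50% | 22 | 11 | 1.03 SD |
| 30% | 13.2, about 13 | 6.6, about 7 | 1.31 SD (1.39 by exact t) |

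For a binary reading, suppose that dense adhesions occur in 50% versus 25% of those scored. Exact Fisher power is 46% at 44 versus 22 and 21% at 22 versus 11.

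**4. Selection on severity.** Assume a normal latent severity (SD 1), a shift δ due to treatment, and reoperation above a threshold k. Take k and δ from the reoperation risks. The mean above k is φ(k)/[1 − Φ(k)] in controls, and −δ + φ(k+δ)/[1 − Φ(k+δ)] with icodextrin.

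At 50% versus 25%: k = 0 and δ = 0.674. The means are 0.798 and −0.674 + 1.271 = 0.597. The difference is 0.201, and 0.201/0.674 = 30% of the true shift.

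| Reoperation risk | True shift | Difference among reoperated | Share kept |
|---|---|---|---|
| 50% / 25% | 0.674 | 0.201 | 30% |
| 25% / 12.5% | 0.476 | 0.100 | 21% |
| 15% / 7.5% | 0.403 | 0.070 | 17% |

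These shares are in whole-population SDs, whereas step 3 uses SDs within the reoperated. Put on that scale with the control SD of the subset (0.60 in the top row, 0.44 in the bottom row):

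- All recurrences reoperated: 0.201/0.60 = 0.33 SD, against 0.74 detectable.
- 30% reoperated (15% / 7.5%): 0.070/0.44 = 0.16 SD, against 1.3 to 1.4 detectable.

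**5. Sensitivity to the mechanism.** Let dense adhesions be present in 50% versus 25% of all patients.

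- Only dense cases reoperated: 100% versus 100% dense among the reoperated, so the difference vanishes.
- 90% of dense and 10% of other cases reoperated: 0.45/0.50 = 90% versus 0.225/0.30 = 75%.
- 80% and 20%: 0.40/0.50 = 80% versus 0.20/0.35 = 57%, close to the true 25 points.

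The distortion therefore depends strongly on how closely reoperation follows severity, which the trial cannot learn from patients who are not reoperated.

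**6. Error rate.** Two independent tests at 0.05, either one counting as success: 1 − 0.95² = 9.75%. Without independence the bound is 10%.

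**The case against.** The strongest reply is that the recurrence endpoint covers all randomised patients, has a reproducible sample size and is untouched. Adhesion findings at reoperation are clinically interesting and are assessed by a blinded surgeon. Rules for combining two primary endpoints, and any power statement for the second, may sit in a full protocol or analysis plan that is not shown. That is fair. Silence on those two matters is not a defect here, and multiplicity can only be a conditional remark. Blinding, however, protects the scoring and not the selection of who is scored.

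Four stronger readings are tempting and are not supported:

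- **The endpoint certainly adds an uncorrected 5% test.** If incidence is 100% in both arms, its test adds no error at all. Inflation needs severity, extent or location to be tested, and success on either primary to be enough. The article states no success rule. If both had to succeed, no correction would be needed, though success would then hang on a small, selected comparison.
- **The endpoint cannot show any effect.** That holds only for incidence, and only if every reoperated patient has adhesions. The scale allows 0, and severity and extent can vary.
- **A true benefit would appear reversed.** The latent-severity model shrinks the difference in every scenario but never changes its sign.
- **Only the worst icodextrin patients are reoperated.** Reoperation may turn on where an adhesion lies or on a surgeon's judgement, and step 5 shows how much this matters.

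**Conclusion.** The point holds. A primary endpoint is defined only in patients selected after randomisation by the other primary outcome. It is not protected by randomisation, and it conflicts with the article's own statement that all randomised patients are analysed. This follows from the text and needs no model.

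The sizes do rest on assumptions. At the planned risks no more than about 44 versus 22 patients would be scored, and fewer if some recurrences are not reoperated; the 30% share behind 13 versus 7 is illustrative. The 30% of the shift that remains at 50% versus 25% depends on a normal latent severity with a reoperation threshold; other mechanisms give anything from no difference to nearly the full one. The error rate of about 10% applies only under an either-endpoint rule with severity or extent tested. The recurrence endpoint and its sample size are unaffected.

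**What to change.** Name ASIO recurrence in all randomised patients as the single primary endpoint. Report incidence, location, severity and extent of adhesions at reoperation as descriptive secondary findings by arm, with the number scored in each and no between-arm efficacy claim.

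If a test related to adhesions is wanted, use reoperation for ASIO (yes/no) in all randomised patients. State how deaths and losses to follow-up are handled, and do not count them as best outcomes. This matters because 65 analysable of 88 enrolled implies 1 − 65/88 = 26% not analysable. For the same reason, ranking everyone without a reoperation as best would not be a safe substitute.

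The cost is a change of endpoint wording and the loss of the adhesion result as a headline claim. The data collected and the sample size stay as planned. If a reoperation test is added, the rule for deaths and losses must be written.

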## Methods

The project is a prospective, randomized controlled investigation performed in the Department of Transplant, General and Emergency Surgery of St. Orsola-Malpighi University Hospital [Bologna, Italy]. The study is designed and conducted in compliance with the principles of Good Clinical Practice regulations.

A computer-generated schedule creates the randomized assignments for the subject and control groups and the results are sealed in numbered envelopes. Participation in the study is requested after diagnosing small bowel obstruction caused by adhesions and determining if the patient fulfills the inclusion criteria [subjects who elect to undergo the surgical laparotomy]. Accordingly to the protocol, the patient signs a document indicating his or her consent and the responsible surgeon discloses the envelope.

If after opening the sealed envelope containing the assignments, the patient declines to enter the trial, the case is excluded from the study [all dropped-out patients are reported].

The responsible surgeon will record the patient's name [and number].

Each group has a sample size of 88 patients [176 patients for the whole study].

All randomized patients [Intention to Treat population] are included in the analysis.

Sample size has been calculated to reach a confidence level of 95% with a power of 80%.

A sample size of 88 patients each group [65 analyzable] is calculated supposing that the ASIO patients [first, second, third or fourth operation for ASIO] have a mean risk of 50% to develop a further episode of ASIO and this risk can be decreased by 25% [from 50% to 25%] with the use of Icodextrin 4%

Inclusion criteria are:

Adult patients [> 18 years]

Submitted to laparotomic surgical procedures for ASIO

Clinical and radiological evidence of adhesive small intestine obstruction

ASA I-III patients

Informed consent

Exclusion criteria

Intrabdominal cancer

Peritoneal contamination

IBD

Positive history of radiotherapy

Patients with an intra-operative findings of different pathology will be excluded from the study

Preoperative data include patient demographics, comorbid conditions [genitourinary, cardiac, pulmonary, gastrointestinal, renal, or rheumatologic] and a detailed history of previous occlusions and surgical procedures.

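### Yearly interim analyses of the primary outcomes share one unqualified p < 0.05 rule; if any look may be claimed, overall error exceeds 5%

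*Protocol article*

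**What the plan says.** All the relevant text is in the Methods section of the protocol article.

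- **Timing.** After Figure 1: "The primary outcomes are assessed every year [interim analysis] up to 5 years after the last enrolled patient". The sentence just before it separately lists the visits at which complications are recorded.
- **Decision rule.** The statistical paragraph that follows assigns ANOVA to continuous data and chi-squared or Fisher exact tests to discrete data. It closes: "Statistically significant differences between study treatments are based on p < 0.05". No other level is given, and no analysis is singled out as confirmatory or described as descriptive.
- **Sample size.** "Sample size has been calculated to reach a confidence level of 95% with a power of 80"%. Patients are assumed to "have a mean risk of 50% to develop a further episode of ASIO", and "this risk can be decreased by 25% [from 50% to 25"%]. The result is "A sample size of 88 patients each group [65 analyzable"].
- **Calendar.** "The study takes approximately 2 years for the inclusion period", and patients are followed for 5 years.

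**The concern.** Taken together, these statements schedule several comparative analyses of the primary outcomes on accumulating data and offer the same 5% threshold to each. If every analysis is an opportunity to declare benefit, the chance that at least one crosses p < 0.05 under no effect is larger than 5%, and the 95% confidence level behind the sample size no longer describes the procedure.

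The trial's main claim is at stake. A significant result at an early look would rest on short follow-up, and possibly on partial enrolment if looks start during the inclusion period. Nothing in the text says that such a result is not to be claimed.

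**Working it through.** **1. Reproduce the plan's own figure.** Inputs from Methods: p1 = 0.50, p2 = 0.25, α = 0.05 (sidedness not stated; two-sided taken, z = 1.96), power 80% (z = 0.8416). The mean risk is 0.375.

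- Without continuity correction: n = [1.96 × √(2 × 0.375 × 0.625) + 0.8416 × √(0.25 + 0.1875)]² / 0.25² = (1.3419 + 0.5567)² / 0.0625 = 57.7, so 58 per arm.
- With continuity correction: (57.7/4) × [1 + √(1 + 4/(57.7 × 0.25))]² = 65.4, that is 66 rounded up, or the stated 65 rounded down.
- 65/88 = 0.74, so 88 allows for about 26% not analyzable.

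The figure is therefore a fixed-sample, two-sided 5% calculation with no allowance for repeated looks.

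**2. Count the looks.** The article does not fix the number. Counting from the last enrolment gives 5. Counting from the start of a 2-year inclusion period gives 2 + 5 = 7.

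**3. Textbook benchmark.** For K equally spaced looks, the quantity is P(|Z_k| > 1.96 for at least one k ≤ K) under no effect. Simulation gives 5.0% for K = 1, about 14.1% for K = 5 and about 16.6% for K = 7.

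**4. Adapt to this trial.** Calendar-year looks are not equally spaced in information. For example, take a 5-year risk of 37.5% and a constant hazard of −ln(0.625)/5 = 0.094 per year. One year after the last enrolment, patients have 1 to 3 years of follow-up. The mean risk by then is 1 − (e^−0.094 − e^−0.282)/0.188 = 0.17. That is 0.17/0.375 = 45% of the final events, against 20% under equal spacing.

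The design was therefore simulated directly under no effect. The assumptions were 65 or 88 per arm, even accrual over 2 years, a 5-year risk of 18–50% in both arms, a constant or early-weighted hazard, and a cumulative 2×2 test at each look with p < 0.05. The chance of significance at one or more looks was:

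| Test used at each look | 5 looks | 7 looks |
|---|---|---|
| Chi-squared, uncorrected | about 11–14% | about 15–20% |
| Chi-squared, Fisher if an expected count is below 5 | about 11–13% | about 11–17% |
| Fisher throughout | about 7–9% | about 7–14% |

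Individual runs moved a point or so either way with the accrual pattern and hazard shape. Under the same assumptions, a single chi-squared test at the end rejects in about 5%.

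**5. What controlling the error would take.** Over 5 equally spaced looks, an O'Brien-Fleming-type boundary leaves about 0.041 for the final test (critical value 2.04); over 7 looks it leaves about 0.039. A Pocock-type boundary needs about 0.016 at each of 5 looks. Treating the final test alone, the step 1 formula with continuity correction gives about 69 analyzable per arm at 0.0413 (against 66 at 0.05) and about 86 at 0.0158. With 65 per arm, the uncorrected approximation to power is:

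- at 0.05: Φ[(0.25√65 − 1.96 × 0.6847)/0.6614] = 84.6%;
- at 0.0413: Φ[(0.25√65 − 2.04 × 0.6847)/0.6614] = 82.5%.

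**The case against.** **The yearly assessment could be a data-collection schedule.** The text says the outcomes are assessed, not tested, and the p < 0.05 sentence sits in a general paragraph on methods. This has some force: testing at every look is read from two sentences together, and no early claim or stopping rule is stated. But visit-level recording is already covered by the preceding sentence. The primary-outcome sentence carries the label of interim analysis and is timed from the last enrolment, which describes an analysis of the trial and not a patient visit.

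**Boundaries and the confirmatory time point usually belong in the analysis plan or full protocol.** That is right, and the absence of a boundary from a condensed article is not the point. The point is that the article itself schedules the interim analyses and itself fixes an unqualified threshold. An adjustment written elsewhere would have to override that sentence.

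**The size depends on assumptions.** This stands. A reader might infer that the trial's actual false-positive rate is some 12–21% and that the 95% level simply fails. The documents do not support that. They do not say that significance at any look counts as success, they leave the number of looks open, and they allow Fisher's test, which suits the sparse early tables and lowers the figure. If only the last analysis decides, the error is about 5%.

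**Conclusion.** The point holds in conditional form. The article plans yearly interim analyses of the primary outcomes, applies one unqualified p < 0.05, and sizes the trial for a single look. Followed as written, with any look open to a claim, the overall two-sided error is above 5% in every scenario examined: about 11–14% for 5 looks and about 11–20% for 7 with chi-squared or chi-squared/Fisher as appropriate, and about 7–14% with Fisher throughout.

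These ranges rest on the any-look condition and on assumed numbers of looks, accrual and event risk. They concern one primary endpoint; also testing the second, adhesions at reoperation, could only add to them. The direction is secure, while the exact size is not fixed by the documents.

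**What to change.** State that there is one confirmatory test of ASIO recurrence, at two-sided 0.05, at the analysis when the last patient has completed 5 years. State also that the earlier yearly analyses are descriptive and carry no significance claim. Record this before any comparison by arm is seen. It costs only wording, and the stated 65 analyzable and 88 randomized per arm keep their 5% level.

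If claims before the end are wanted, fix the number and timing of the looks and use an O'Brien-Fleming-type alpha-spending boundary. The level at each look should be computed from the information actually accrued, because a tabulated set of levels for equally spaced looks would not fit this calendar. The final level would be about 0.04. The cost is about 2 points of power at 65 per arm (84.6% to 82.5% in the approximation above), or about 69 analyzable per arm in place of 65, which is within the 88 randomized only if the loss is smaller than the 26% allowed for.

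### ASIO recurrence is to be tested only as a crude proportion, although follow-up will be unequal at the yearly looks and probably incomplete at five years; a time-to-event analysis fits the design better

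*Protocol article*

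**What the plan says.** All of the following is in the Methods of the protocol article.

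- First primary endpoint: "To evaluate the therapeutic role of Icodextrin 4% to reduce ASIO incidence".
- Analysis: "The data generated by this study are analysed in two ways", namely ANOVA for continuous data and, for the rest, "Discrete data are analysed by the chi-squared test or Fisher exact test, as appropriate". The criterion is "Statistically significant differences between study treatments are based on p < 0.05". No time-to-event method is named.
- Follow-up: "The patients are followed-up for 5 years". The calendar of analyses is "The primary outcomes are assessed every year [interim analysis] up to 5 years after the last enrolled patient".
- Accrual: "The study takes approximately 2 years for the inclusion period".
- Size: "A sample size of 88 patients each group [65 analyzable", for a risk of 50% falling to 25%, with no time horizon attached. All randomised patients are to be analysed.
- Patients may withdraw at any time. Some may also leave the study around surgery: refusal after the envelope is opened, a different pathology found at operation, or bowel leakage.

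**The concern.** A chi-squared or Fisher comparison of incidence needs each patient's recurrence status over one common period. The design does not provide this at the yearly looks, where patients recruited early have been observed much longer than those recruited late. It probably does not provide it at the final analysis either, because the sample size itself allows for patients without a usable outcome.

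A patient who leaves event-free at 2 years then has to be counted as recurrence-free or dropped, unless an imputation rule is added. The first choice pushes incidence down and the second pushes it up. Either way the two years of observation are not used for what they are. At stake are the reported recurrence rates, which are the main clinical result, and some protection against unequal loss between arms.

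**Working it through.** **1. The plan's own figure.** Inputs: 50% against 25%, 80% power, 95% confidence taken as two-sided 5% (sidedness is not stated).

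n = [1.96·√(2·0.375·0.625) + 0.8416·√(0.25 + 0.1875)]² / 0.25² = 57.7 per arm.

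With the continuity correction: (57.7/4)·[1 + √(1 + 4/(57.7·0.25))]² = 65.4, which matches the 65 analysable. The design calculation is therefore a fixed binary comparison with no time axis.

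**2. Implied share without a usable outcome.** 1 − 65/88 = 26.1%. Conversely, 65/0.74 = 87.8, or 88.

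**3. Unequal follow-up at a yearly look.** One year after the last entry, follow-up runs from 1 to 3 years. If 50% and 25% are 5-year risks with constant hazards (assumption), the 1-year risks are 1 − 0.5^0.2 = 12.9% and 1 − 0.75^0.2 = 5.6%; the 3-year risks are 1 − 0.5^0.6 = 34.0% and 1 − 0.75^0.6 = 15.9%. In simulation (88 per arm, uniform entry over 2 years, 26% loss by year 5) the crude proportions at this look average 22.6% and 10.2%, which are the risk at no defined time. Kaplan-Meier at 1 year gives 13.0% and 5.6%.

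**4. Final analysis, 5-year window per patient.** Assume the 26% is exponential loss, independent of recurrence and equal in the arms. Over 5 years the cumulative hazards are 0.693 (control), 0.288 (icodextrin) and 0.301 (loss).

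- Recurrence observed, control: 0.693/(0.693 + 0.301) × (1 − 0.5·0.74) = 43.9%.
- Recurrence observed, icodextrin: 0.288/(0.288 + 0.301) × (1 − 0.75·0.74) = 21.7%.
- Completing 5 years event-free: 0.5·0.74 = 37.0% and 0.75·0.74 = 55.5%.
- Lost event-free patients dropped: 43.9/(43.9 + 37.0) = 54.3% and 21.7/(21.7 + 55.5) = 28.1%. This set averages about 71 and 68 patients per arm.

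| Method | Control | Icodextrin | Difference | Ratio | Power (simulated) |
|---|---|---|---|---|---|
| True 5-year risk | 50.0% | 25.0% | 25.0 | 0.50 | – |
| Lost counted as event-free | 43.9% | 21.7% | 22.2 | 0.49 | 88.6% |
| Lost event-free dropped | 54.3% | 28.1% | 26.1 | 0.52 | 88.7% |
| Kaplan-Meier / log-rank | 50.0% | 25.0% | 25.0 | 0.50 | 90.4% |

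The powers come from 6,000 simulated trials; further runs put log-rank at 90.6% and 90.8%.

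**5. Type I error (simulated, true risk 50% in both arms).** With equal loss, chi-squared rejects in 4.4% to 5.7% of trials and log-rank in about 5%. With 16% against 36% loss (assumed for illustration), and taking both a fixed 5-year window and 5 to 7 years of observation, chi-squared rejects in 11.0% to 13.9% with lost patients counted as event-free and in 7.7% to 8.6% with them dropped. Log-rank stays at about 5%.

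**6. Whether the planned size supports a log-rank test.** Under proportional hazards HR = ln 0.75/ln 0.5 = 0.415. Events needed (Schoenfeld): 4·(1.96 + 0.8416)²/(ln 0.415)² = 41; Freedman's formula gives 46. Expected with the assumed loss: 88 × (0.439 + 0.217) = about 58. No larger sample is needed.

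**The case against.** - **26% loss to follow-up is not stated.** The article gives only 65 analysable of 88. Part or all of the gap may be perioperative removals. Such patients have almost no follow-up to censor, so a log-rank test cannot repair their absence. This stands, and the sizes in step 4 are therefore conditional.
- **A 5- to 7-year window is not established.** A reader might infer that the two follow-up sentences conflict and that early patients are counted for up to 7 years. Without any loss that would give crude figures of 56.4% and 29.1%. But the sentences can be read together: 5 years each, with analyses continuing until the last patient completes 5 years. On that reading staggered entry affects only the yearly looks. With no loss the final chi-squared is then unbiased, with 94% power against 94% for log-rank.
- **The comparison of arms is not broken.** A reader might infer an invalid test or a serious loss of power. With equal loss the error rate holds, the ratio hardly moves and the power gap is about 2 points. Nothing in the article suggests unequal loss.
- **Dropping or counting are not the only options.** A 5-year proportion with imputation can be valid, and missing-outcome rules may properly sit in a full protocol or SAP. Their absence is not the point here. The point is that the article does fix a test, and that test takes no account of how long each patient was observed.

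**Conclusion.** The point holds in moderate form and should be acted on. The article commits the recurrence endpoint to a crude proportion test, in a design with staggered entry, yearly analyses, free withdrawal and an expected shortfall in usable outcomes.

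At the early looks the crude incidence refers to no defined period, whatever the loss. At 5 years it would be about 3 to 6 percentage points off, downward or upward according to how lost patients are handled. For the control arm the two versions are about 10 points apart (43.9% and 54.3%).

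The 5-year sizes assume that 50% and 25% are 5-year risks, that recurrence and loss times are exponential and independent, that all of the 26% is loss during follow-up, and that there are no deaths. If much of the 26% leaves around surgery, the bias that censoring can correct is smaller. The documents do not support a claim of inflated type I error without an added assumption of unequal loss.

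**What to change.** Define the primary as time from randomisation to first ASIO recurrence, censored at last contact and at 5 years. Include every randomised patient. Compare arms by log-rank test with a Cox hazard ratio, and report 5-year cumulative incidence by arm with death without recurrence as a competing event. State that the phrase about 5 years after the last enrolment marks the calendar end of a single 5-year window per patient. Use the same method at the yearly looks; this does not settle repeated testing, which is a separate matter.

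Cost: no extra patients. The date of recurrence (admission) has to be recorded, which the article does not say is done. The visit schedule it gives, for other complications, is yearly after 6 months, so dates taken from such visits would be known only to within a year. The hazard ratio also assumes proportional hazards; the cumulative incidence does not.
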